### 11.1.1 Initial SQL Rule-Based Translation of Case Definitions

Based on consensus results, initial case definitions for each phenotype will be developed and translated into SQL rule-based algorithms within the EHR database schema of the primary site. These initial definitions/queries will then be used in the sampling strategy to build the training and validation data cohort.

### 11.1.2 Development of Training and Internal Validation Cohort

#### 11.1.2.1 Study Setting

The training and internal validation cohort will be derived from patients presenting to 1 of 4 EDs over a 6-year time period (March 2013 through March 2019). All EDs are part of a single health

care system. One is an urban, academic, level 1 trauma center with 100,000 annual visits; the second ED is an urban level 2 trauma center with 90,000 annual visits, the third ED is a community-based, urban ED with an annual census of approximately 65,000 annual visits, and the fourth ED is a suburban free-standing community-based center with approximately 25,000 annual visits.

#### 11.1.2.2 IRB

For this part of the study, we will use the primary site institutional review board (Yale Human Research Protection Program) and apply for waiver of the requirement for informed consent. We will exclude all patients who have previously indicated the desire to opt out of EHR-based research within the primary site (a table of these patients is included within the primary site database).

#### 11.1.2.3 Sampling strategy

Because the prevalence of potential phenotypes within the general population is low, simple random sampling from the entire population would require a prohibitively large sample size. Moreover, machine learning methods often are enhanced through better balanced datasets. We will therefore randomly oversample from each phenotype strata to ensure adequate numbers of patients with positive phenotypes as determined by sample size calculations. Initial phenotype sampling will be achieved by application of inclusion/exclusion rules developed through the case definitions.

#### 11.1.2.4 Sample Size determination

Following conventional machine learning methodology, we will randomly partition the data into 80% training and 20% validation sets. We will base our sample size determination on the validation cohort size.

Previous literature has indicated that ICD codes have general high specificity (few false positives) for disease entities within EHR systems, but low sensitivity (large number of false negatives). Development of phenotypes often significantly improve the sensitivity while maintaining specificity. Conservatively, we estimate that we will be able to achieve a specificity of 95% and sensitivity of 70%. We assume 50% prevalence due to oversampling for each phenotype, 80% power, and significance level of 0.05. Based on these assumptions we estimate needing 75 cases per phenotype in the validation cohort to achieve a one-sided lower confidence level limit of 15%. For the total cohort, based on the 80/20 split, we will need ~ 375 cases per phenotype. We additionally will optimize estimation of sensitivity and specificity in the setting of verification bias using the methods developed by Begg and Greens.

We will continually monitor the performance of the development model as its dependence on the sample size through learning curves. If through visual inspection, the performance of the development model plateaus prior to reaching the full sample size, we will stop further data collection on the development data set.

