#### **4. Development and validation of EHR ED opioid-related phenotypes component**

In this component, we will develop EHR phenotypes of opioid-related illnesses that accurately and automatically characterize patient conditions, enhance the ability to actively monitor and surveil, and better identify representative samples and patients potentially eligible for study inclusion, leading ultimately to an enhanced inclusion and understanding of opioid-related conditions. At the primary Yale New Haven Health System sites, the phenotypes (rules- and machine learning-based) will be iteratively developed and internally validated. The rules-based phenotype will be mapped to a common data model and externally validated at 4 trial sites.

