#### *11.1.3.5 Selection of Corpora*

For the annotation task we will select for each ED encounter the ED provider note, nursing notes, and the most recent discharge or primary care note. Within these texts we will adhere to span level, as opposed to document level, phenotype classification.

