#### *11.1.5.3 Analysis with Supervised Machine Learning*

Discovering multiple phenotypes within an encounter can be framed as a multilabel classification problem. Multilabel classification assigns to each sample a set of target labels. In our context, this can be thought as predicting several phenotype properties of an encounter that are not mutually exclusive. We will assess a variety of machine learning methods within the multilabel classification task (e.g., ridge regression classifier, support vector machines, random forest, deep neural networks).

We will explore the use of several different features sets within the machine learning classifiers. A grid search with 10-fold cross-validation will be performed on the training dataset with examination of the classifiers and tuning performed within promising hyperparameter ranges. Then the AUC ROC curve scores will be compared to find the best classifiers, and the hyperparameters further tuned. A tournament-style process will be used to reduce the number of classifiers and hyperparameters through several iterations, until only a single best classifier and set of hyperparameters remain.

Discrimination of the ML-models will be evaluated with AUC ROC curves and 95% confidence interval (CI). Model calibration will be measured visually with calibration plots and formally tested with the Hosmer-Lemeshow goodness-of-fit test. Test characteristics including total accuracy, sensitivity, specificity, negative predictive value (NPV), and positive predictive value (PPV) will be

examined to compare between NLP classifiers and the rule-based approach on the internal validation data set. Adding the ML-based approach to the rule-based approach will be examined for improved performance using the net reclassification improvement (NRI) and integrated discrimination improvement (IDI) measures. As mentioned above, a learning curve will be generated to investigate the effect of sample size on classifier performance as an approach to assess adequacy of statistical power.

Throughout the development and validation of the phenotypes, we will adhere to general coding practices to ensure quality including aspects that ensure readable, reusable, and testable components that are all side effects of writing modular code. Due to the limited size of the project we will forego more sophisticated techniques used when collaborating including pair programming and issue tracking.

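### The EHR phenotype plan does not keep a patient's repeat ED visits together when it splits the data, so training and validation sets can share patients and flatter the machine-learning results

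*Combined protocol and SAP*

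**What the plan says.** All the relevant text is in the protocol; the SAP leaves the EHR phenotype analyses to the Lead Node.

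- **Source (11.1.2.1).** The cohort is "derived from patients presenting to 1 of 4 EDs over a 6-year time period", from March 2013 to March 2019, all in one health system.
- **Sampling (11.1.2.3).** The team will "randomly oversample from each phenotype strata to ensure adequate numbers of patients with positive phenotypes".
- **Split (11.1.2.4).** "we will randomly partition the data into 80% training and 20% validation sets". The section asks for 75 cases per phenotype in validation and about 375 in total.
- **Text used (11.1.3.5).** The team will "select for each ED encounter the ED provider note, nursing notes, and the most recent discharge or primary care note".
- **Unit classified (11.1.5.3).** The task is described as "predicting several phenotype properties of an encounter that are not mutually exclusive".
- **Tuning (11.1.5.3).** "A grid search with 10-fold cross-validation will be performed on the training dataset". The same section compares the ML/NLP classifiers with the rules on the internal validation set, using test characteristics, net reclassification improvement (NRI) and integrated discrimination improvement (IDI).
- **External validation (2.2.1, component 4).** "The rules-based phenotype will be mapped to a common data model and externally validated at 4 trial sites". Section 11.0 says the same.

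Section 11 contains no rule that keeps a patient's encounters together, none that limits a patient to one encounter, and no allowance for repeat encounters in the sample size or the confidence intervals.

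**The concern.** If encounters are assigned at random and a patient has more than one in the sample, some validation encounters belong to patients the classifier has already seen. Their notes share history, vocabulary and sometimes a whole document: two nearby visits can have the same latest discharge or primary care note attached. The features are medical concepts, single words and word pairs, so a classifier can gain by recognising the patient rather than the condition. Validation then measures performance on a mixture of new and familiar patients, whereas the intended use is on new patients. Shared patients across folds create the same problem during tuning and tend to favour settings that memorise.

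At stake are the internal AUC, sensitivity and specificity of the ML/NLP phenotypes and the NRI and IDI that are meant to show what they add. Hand-built rules have far less capacity to memorise individuals, so the comparison would tilt toward ML. The documents state no external test of the ML models that would reveal this.

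**Working it through.** **1. The plan's own figures.** Inputs from 11.1.2.4: expected sensitivity 70%, 80% power, alpha 0.05, and a lower limit given as 15%, read here as 15 points below 70%, that is 55%. An exact one-sided binomial test of 0.70 against 0.55 stays at or above 80% power from n = 73; n = 75 gives 84.3%. The total is 75 / 0.20 = 375, so training holds 0.80 × 375 = 300 cases per phenotype. The figures reproduce, but they treat cases as independent.

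**2. Repeat visits already in the sample.** If m visits by one patient are all sampled and split at random 80/20, a validation visit has at least one companion in training with probability 1 − 0.2^(m−1):
- m = 2: 80%
- m = 3: 96%

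For 10 folds the expression is 1 − 0.1^(m−1), giving 90% and 99%. A simple random split therefore does little to separate a patient's visits.

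**3. How often repeats would be sampled.** The documents give no repeat-visit rate, so this step rests on assumptions. Let E be the pool of qualifying encounters for one phenotype, T = 300 the training cases, and K the number of other qualifying visits by a validation patient. The share of validation cases with a patient in common with training is approximately f = 1 − (1 − T/E)^K.

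For scale, the stated annual volumes give (100,000 + 90,000 + 65,000 + 25,000) × 6 = 1,680,000 visits. Pools of 10,000 and 40,000 are 0.6% and 2.4% of these.

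| E (assumed) | K (assumed) | f |
|---|---|---|
| 40,000 | 3 | 1 − 0.9925^3 = 2.2% |
| 10,000 | 10 | 1 − 0.97^10 = 26.3% |

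**4. Common against rare phenotypes.** Same formula, with the pool set by an assumed prevalence among the 1.68 million visits, for a patient with 2, 5 or 10 qualifying visits (K = 1, 4, 9):
- Prevalence 1% (E = 16,800, T/E = 0.0179): 1.8%, 7.0%, 15.0%
- Prevalence 0.1% (E = 1,680, T/E = 0.179): 17.9%, 54.5%, 83.0%

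Overlap is small when a common phenotype is thinly sampled and large when a rare one is nearly exhausted or the patient visits often.

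**5. Effect on precision if repeats are kept.** With a patient-level split, the design effect is 1 + (m − 1) × ICC, where m is now the mean number of sampled visits per patient and ICC the within-patient correlation (both assumed):
- m = 1.2, ICC = 0.2: 1.04 × 75 = 78 validation cases, 390 in total
- m = 1.5, ICC = 0.5: 1.25 × 75 = 93.75, so 94, and 470 in total
- m = 2, ICC = 0.5: 1.5 × 75 = 112.5, so 113, and 565 in total

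With one encounter per patient the design effect is 1, and 75 and 375 stand.

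**The case against.** The strongest reply is that the split section names no unit. It speaks of data and cases, and the setting and sampling sections speak of patients. A cohort with one visit per patient fits that wording, and then nothing leaks. This stands to the extent that the unit is inferred from the labelling, text-selection and modelling sections, all of which work on encounters. It does not remove the point, because nothing in section 11 imposes one visit per patient and the stated random split permits overlap.

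Second, section 11 calls itself an overview, and development runs under a separate institutional approval, so fold construction may be specified elsewhere. That is possible. If so, adding it here costs nothing.

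Third, the phenotypes carried forward are the rules-based ones, which are tested at four other sites against prospective screening. The ML work mainly supplies features for the rules and an indication of the best accuracy attainable. This also stands, and it limits the harm to the internal ML/NLP results. Section 11.5 refers to EHR phenotypes in general, but it does not say that the ML models go to external validation.

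A reader might go further and infer that patients with opioid-related illness return so often that most validation cases are contaminated, or that the training cases of all phenotypes can be counted together against the pool of one. The documents give no return rate. Summing training cases also requires enlarging the pool, or allowing for encounters that count toward several phenotypes.

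**Conclusion.** The concern holds in a limited form. As written, the split and the folds allow one patient's encounters on both sides, which would bias the internal ML/NLP accuracy and the NRI/IDI comparison in favour of ML wherever repeat encounters are sampled and the classifier exploits shared text.

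The amount of bias cannot be computed from the documents. The 2% to 26% overlap for one phenotype rests on the assumed pools and return visits above. It is a share of cases, not a change in AUC or sensitivity; converting it would need a further assumption about how much better familiar patients are classified. The bias is zero with one encounter per patient, probably small for common phenotypes sampled thinly, and larger for rare phenotypes or frequent visitors.

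It would be wrong to conclude that Aim 4 as a whole is invalid or that the trial is touched. The rules-based phenotypes have their own external validation, and no randomised comparison, safety result or trial sample size depends on this step.

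**What to change.** - **Section 11.1.2.4:** state that patients, not encounters, are randomly partitioned 80/20, so that all of a patient's encounters fall in one set. Alternatively, sample at most one encounter per patient, which leaves 75 and 375 unchanged.
- **Section 11.1.5.3:** state that the 10 folds are formed by patient.
- **If repeat encounters are kept:** compute intervals for sensitivity, specificity, AUC and the ML-versus-rules comparison with patient clustering, for example a patient-level bootstrap.

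The cost is about a sentence in each section and grouped splitting in the code. Splitting by patient needs no extra chart review. The split will be only approximately 80/20, reported ML performance may be slightly less favourable, and precision will be somewhat lower than planned if repeat visits stay in, unless more cases are labelled.

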### 11.1.3 Annotation for NLP

#### 11.1.3.1 Overview

We will use annotation as a means to label opioid-related phenotypes within encounters, identify important text features of these phenotypes, and highlight conceptual relations between these phenotypes. We will use a light annotation framework within the MATTER cycle. Features discovered in these steps will inform the rule-based and machine learning based phenotype definitions.

#### 11.1.3.2 MATTER Cycle

For annotation tasks and incorporation of annotations into machine learning categorization we will adhere to the MATTER cycle (Figure 2). The model can be described as set of three components  $M = (T, R, I)$  where  $M$  is the model,  $T$  is the set of terms being used,  $R$  is the relations between terms, and  $I$  is the interpretation of the terms and relations. Model and annotation development will go through an iterative process on a sample of documents, referred to as MAMA (model annotate model annotate), where problems are worked out and the final versions are determined. The training, testing, and evaluation steps are where the machine learning algorithm is taught to recognize features, tested and evaluated. Revise is final step at which the entire process is reviewed.

##### 11.1.3.2.1 Figure 2: MATTER Cycle

[figure not shown]

#### 11.1.3.3 Annotation Framework

We will adhere to a light annotation framework to optimize resources on the specific task of phenotype classification. The concept of light annotation task (for domain specific annotation) is a linguistically under-specified, task- and domain-specific model that potentially overlaps with a full and more resource intensive annotation task. Underspecified tags within light annotation tasks do not supply full syntactic or semantic content but instead can be used to indicate more broadly the areas of interest (e.g., is this patient homeless). A light annotation task is used to quickly capture domain specific knowledge in a corpus as it relates to a research question but does not require trained investigators to perform intensive annotation. The end result is a dataset that

represents complex information but that is itself not complex and that is in a format that will not conflict with any tags or labels that might be applied in future tasks.

#### *11.1.3.4 Development of Light Annotation Schema*

We will develop a light annotation schema using a multi-staged approach. First, we will leverage the phenotypes and concepts developed in Delphi consensus process and record general, statements that declare in broad terms the annotation goals. As an example, the annotation goal could be, “Does this patient have opioid withdrawal?” and, “What parts of this text provide that information?” Next, we will use a multi-stage iterative coding approach to sample sets of texts to enumerate specific variables and relationships to be considered when annotating. Iterative coding has been applied to the biomedical domain for many studies including discovery of clinical conditions in emergency medicine notes. The iterative coding approach involves reading and re-reading text to develop a schema/codebook that can be used for light annotation. Based on prior literature of successful annotation schema development, we will randomly select 15 encounters from each phenotype scenario to develop the annotation schema. We will use randomly split the encounters for creation of the annotation schema and to validate the schema.

We will adhere to the method of text-bound annotation (i.e., we will associate all annotation with actual expression in text) to ensure a higher likelihood of inter-annotator agreement. We anticipate annotation tags to cover entities/relationships pertinent to phenotype discovery, modifier tags, link tag (modifier to phenotype discovery tag, tags between phenotypes linking their relationships), non-consuming tags.

#### *11.1.3.5 Selection of Corpora*

For the annotation task we will select for each ED encounter the ED provider note, nursing notes, and the most recent discharge or primary care note. Within these texts we will adhere to span level, as opposed to document level, phenotype classification.

#### *11.1.3.6 Annotation Tool*

We anticipate using the Multipurpose Annotation Environment (MAE) lightweight general-purpose multi-modal annotation tool written in JAVA. MAE handles diverse data and annotation, is multi-level, simple, customizable, has quality assurance components, and is convertible to other formats. We also anticipate performing annotation adjudication through the MAI interface which provides a simple interface, built on the same basic code as MAE, for users to load and compare annotations on the same document and determine which tags should be included in the gold standard.

#### *11.1.3.7 Annotators*

Annotators will be research assistants with prior experience in emergency medicine research. Annotators will be trained by experts in substance abuse research, emergency medicine and linguistic analysis.

#### 11.1.3.8 Annotation Analysis

We will measure the schema's completeness, the annotators ability to apply the schema with high agreement (measured by kappa statistics). We will also analyze strict and overlapping metrics for annotation adjudication (e.g., precision, recall, f-measures).

### 11.1.4 Rules-Based Phenotype Development

Rule-based EHR phenotype algorithms will be developed based on case definitions developed through the Delphi consensus process. Rule-based systems remain one of the most popular computational phenotyping methods in the field due to their straightforward construction, relative ease in implementation, and reasonable levels of accuracy.

We anticipate using a variety of clinical data types including medications, diagnostic codes, and laboratory studies. We will, therefore, iteratively refine the phenotype rules-based algorithms through comparison to the initial chart review and gold standard labeling of the training cohort using collaboration among subject matter expert cohort leads, informaticians, and data analysts. During the refinement process various cutoff points for data elements with multiple values will be explored as well as the inclusion/exclusion of specific data elements. Continuance of the refinement process will be balanced by consideration of quality and feasibility of the individual data elements as well as the complexity of the algorithm. Within the iterative process, we will explore various time-sequences or temporal scopes for application of the rules for each phenotype (e.g., looking at the last month vs. year of labs, diagnoses).

Analysis of the rule-based phenotypes will follow a similar plan as the ML/NLP phenotype development described below. Internal validation will examine various test characteristics (e.g., sensitivity, specificity, accuracy) of each phenotype.

### 11.1.5 ML/NLP-Based Phenotype Development

#### 11.1.5.1 Overview

Natural language processing (NLP) plays a complementary and important part in information extraction where clinical notes potentially contain rich information needed for phenotype identification. Rule-based systems often need many complex attribute-specific rules, which may be too rigid to account for the diversity of the language expression. As a result, rule-based systems may exhibit high precision, but low recall. We will use NLP for two tasks related to phenotype development and evaluation. First, previous studies using expert consensus and rule-based development encountered gaps in identification of the metadata of relevant data elements.

To improve identification and potentially discover new metadata elements for rule-based deployment, we will extract UMLS concepts and all possible unigrams and bigrams from ED clinical reports and further rank their relevance to OUD identification using statistical feature selection techniques. We will also support feature identification through light annotation tasks. Those elements which have structured counterparts, are feasible, are valid, and improve the rules-based performance will be incorporated into the final algorithms.

We will also assess the additive value of NLP on our rule-based phenotype algorithms by developing a hybrid algorithm using machine learning incorporating the light annotation. This will serve several purposes, including representing a potential upper bound of phenotype accuracy and identifying data concepts and elements which exist only in unstructured domains but are relevant to phenotype identification.

